### Trial assessments

#### Participant identification

Potential participants will be identified from EDs/AMUs or other acute settings and approached either during their ED/AMU or hospital stay or contacted after discharge and invited to take part in the study.

#### Participant consent

Potential participants will be given a Participant Information Sheet (PIS). Potential participants will be randomised within 72 hours of their hospital attendance. If a patient has been discharged from the hospital, then they will be contacted by the local clinical team or research team (if part of the clinical team), and a copy of the PIS will be emailed or posted out to the patient. The PIS will also be available on the trial website. A delegated member of the local study team will seek verbal consent over the telephone and will sign the consent form on behalf of the participant. The original consent form will be filed in the Investigator Site File and a copy will be sent to the participant. Alternatively, the patient can attend the hospital with travel expenses, to provide written informed consent in person. The ambulatory ECG device can be sent to the participant’s address or collected from the local study team if randomised to the intervention arm. Each participating centre will upload screening information of non-identifiable potentially eligible patients who were approached to participate in the study, onto the study database. Participants are free to withdraw from the study at any point or can be withdrawn by the investigator.

Participants will have an electronic case report form completed at randomisation (table 2). Recruited participants regardless of allocation group, will be referred for syncope assessment as per local service protocol and subsequent investigations will be arranged at the discretion of the treating clinician. Participants randomised to the intervention arm will be fitted with a 14-day ambulatory heart monitor (Preventice BodyGuardian Mini) applied by the study team as soon after randomisation as possible. The ambulatory ECG monitor will be placed on the participant’s chest wall over the sternum, connected directly to an ECG electrode sticker (figure 2). The participant’s skin does not require shaving but is cleaned prior to attaching the device, which are easily removed by the participant after 14 days. The monitor can be worn by both women and men.

**Table 2 T2:** Study assessments

Assessment	Screening	Day 1 baseline	Monthly	90 days	Every 3 months	1 year	2 years
**Window of time for evaluation**	**n/a**	**n/a**	**±14 days**	**±14 days**	**n/a**	**±30 days**	**±30 days**
Assessment of eligibility criteria	X						
Informed consent	X						
eCRF completion including demographic data and contact details	X						
Routine clinical care (eg, ECG)	X						
Randomisation		X					
Intervention group participants fitted with a 14-day ambulatory heart monitor		X					
Referral for syncope assessment and standard care monitoring as per local service protocol to be seen ideally within 4–6 weeks of the index event especially if discharged from ED or if this did not occur during index admission		X					
EQ-5D-5L questionnaires		X				X	X
NHS resource usage data from routine hospital electronic healthcare records extracted by the local study team)				X		X	X
Participant contacted on a 4-weekly basis via automated text message, email or phone with a link to a brief web-based questionnaire asking for the number of syncope events experienced since last response, and the number of GP attendances for any reason			X				
Participants not responding for 3 consecutive months to receive phone call from central study team to collect missing data, ensure no syncope episodes have occurred and to encourage continued future engagement. Participants with a mean of 5 or more episodes/month will also receive a phone call from the central study team to ensure that participants are recording true syncope events and are seeking appropriate medical advice					X		
Participant satisfaction questionnaire						X	

eCRF, electronic case report form; ED, emergency department; GP, general practitioner.

**Figure 2 F2:**
[figure not shown]
14-day ambulatory heart monitor (Preventice BodyGuardian Mini).

Participants will be required to press the button on the heart monitor after any syncopal event. They will also record symptomatic episodes in a paper diary. The participant will wear the ambulatory ECG monitor for a maximum of 14 days after which they will remove and return it in a prepaid envelope to Preventice UK. The monitor will be reported by a cardiac physiologist, shared with the participant’s local study team, placed in the participant’s health record and shared with the participant’s treating clinician. Treatment of device findings will be at the discretion of the treating clinician at each site. The participant’s general practitioner (GP) will be informed that the participant has been enrolled in the study and will be informed of the results of any ECG investigations via routine hospital clinical correspondence. Participants will be informed of the results of any ECG investigations via routine hospital clinical correspondence. Any study participant with a serious arrhythmia (box 2) on the ECG report will be contacted as soon as possible by the local team and managed appropriately according to local policy.

All participants will be contacted on a 4-weekly basis ±14 days for 2 years via automated text message or email (whichever they prefer) with a link to a brief web-based questionnaire asking for the number of syncope events experienced since their last response and how many of these they attended hospital for. Those who are unable to access digital forms of communication will receive phone calls. They will also be asked since their last response how many times they have visited their GP practice for any reason including all face-to-face, telephone and online consultations. This will import directly into the central ECTU study database. This patient-reported data will be used to inform the primary endpoint. The small number of participants unable to access digital forms of communication and participants not responding for 3 consecutive months will receive a phone call from the central study team (blinded to participant’s study arm allocation) to collect missing data, ensure no syncope episodes have occurred and to encourage continued future engagement. Participants with a mean of 5 or more episodes/month will also receive a phone call from the central study team to ensure that participants are recording true syncope events and are seeking appropriate medical advice.

We were very thoughtful about the potential impact of COVID-19 when designing this study including ensuring ambulatory ECG monitors can be sent directly to patients and designing participant follow-up to ensure no additional research related hospital visits are required.

Participants will also be contacted at one and 2 years±30 days, by the central study team (blinded to participants study arm allocation) to complete a quality-of-life questionnaire. In the event of non-response, participants will be contacted on up to three occasions. The participants’ involvement in the study will cease at 2 years. Endpoint data including NHS resource usage will be extracted by the local study team from routine hospital electronic healthcare records at 90 days, 1 and 2 years and will be entered into a bespoke database. ECTU will collect and clean primary data and perform primary and secondary analyses.

#### Timelines

The study started on 1 August 2021 and the first patient was recruited on 15 July 2022. Recruitment is planned to end on 31 December 2023, the with study completing on 31 July 2025.

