### Randomisation and interventions

Randomisation will be performed using a web-based randomisation service to ensure allocation concealment, managed by Edinburgh Clinical Trials Unit (ECTU). The allocation sequence will be created by an ECTU database programmer using computer-generated pseudo-random numbers. Participants will be randomised, 1:1, between the two study arms. Stratification by site will be used to ensure there will not be a significant imbalance between the number randomised to intervention and control at any site. Stratification by other site-level characteristics will not be performed.

Standard care will include all care usually given to unexplained syncope patients at each participating site along with some form of standard care monitoring such as but not limited to wired inpatient telemetry, Holter style monitoring or implantable ECG recorder. The study will be conducted over 4 years. Recruitment will take place over 18 months. Intervention group participants will be fitted with a 14-day ambulatory heart monitor. All participants will be followed up for 2 years after index event.

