#### Data analysis plan

The primary outcome, number of self-reported episodes of syncope in the 12 months following randomisation, will be analysed by negative binomial regression. The primary outcome event rate ratio (14-day ambulatory heart monitor vs standard care) will be reported with its 95% CI. An offset term for follow-up duration will be included to account for participants with partial follow-up.

The secondary outcomes for the number of syncope episodes at 90 days and 2 years, will be analysed similarly. Binary secondary outcomes will be analysed by logistic regression, reporting the OR (14-day ambulatory heart monitor vs standard care) and its 95% CI. Full details of analysis, including the estimand(s) of interest and methods for handling missing data, will be written into a Statistical Analysis Plan, which will be finalised prior to database lock without knowledge of the unblinded treatment allocations.

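### The stated completion date of 31 July 2025 leaves the last recruits at most 19 months of follow-up, although every participant is promised 2 years

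*Protocol article*

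**What the plan says.** The promise of 2 years appears in several places in the protocol article.

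- Randomisation and interventions: "All participants will be followed up for 2 years after index event". The same section gives 4 years for the whole study and 18 months for recruitment.
- Trial assessments, text after Figure 2: "All participants will be contacted on a 4-weekly basis ±14 days for 2 years"; "Participants will also be contacted at one and 2 years±30 days"; "The participants’ involvement in the study will cease at 2 years". Records are also to be extracted at 2 years, and Table 2 gives the 2-year assessment a window of 30 days either side.
- Secondary endpoints: 2-year versions are set for cost-effectiveness, syncope counts (self-reported and from records), recurrence, clinically significant arrhythmia, ECG/symptom correlation, all-cause death, and tests and interventions.

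The calendar is in Timelines: "The study started on 1 August 2021", "the first patient was recruited on 15 July 2022", and then "Recruitment is planned to end on 31 December 2023, the with study completing on 31 July 2025".

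On analysis, the Data analysis plan gives the primary count model an offset for follow-up duration and treats the 2-year counts similarly. For the rest, "Binary secondary outcomes will be analysed by logistic regression". Estimands and missing-data methods are left to the SAP.

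**The concern.** Recruitment closes 19 months before the study does, yet each participant is to be followed for 24. The two statements cannot both be carried out, and nothing in the article says that late recruits will have shorter follow-up.

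At stake are the 2-year secondary endpoints. For late recruits, the last part of the 4-weekly reporting, the 2-year record extraction and the 2-year EQ-5D would fall after the study has closed. These gaps come from the calendar and not from participants dropping out. Questionnaires that are never sent cannot be recovered later.

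**Working it through.** **Inputs.** From Timelines: study start 1 August 2021, first recruitment 15 July 2022, end of recruitment 31 December 2023, completion 31 July 2025. From Trial assessments and Table 2: 2 years of follow-up, window ±30 days. From Sample size: 2234 participants. The recruitment date stands in for the index date; participants are randomised within 72 hours of attendance, so this makes little difference.

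**The plan's own figures.**
- Duration: 1 August 2021 to 31 July 2025 is 48 months, which agrees with the stated 4 years.
- Sample size: n per group = (1.960 + 1.282)² × (1/1 + 1/0.85 + 2 × 0.25) / (ln 0.85)² = 1064.8, against 1064 stated; 1064 × 1.05 = 1117. It rests on 1-year counts, so this issue does not touch it.

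**Follow-up of the last recruit.** 31 December 2023 to 31 July 2025 is 578 days; 578 / 30.44 = 19.0 months. Two years end on 31 December 2025, 153 days after completion. With the +30-day window, the date is 30 January 2026.

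**Study months needed.**
- Interim analysis section: the 18th month of recruitment is the end of study month 25. 25 + 24 = 49, already more than 48.
- Timelines: 31 December 2023 is the end of study month 29. 29 + 24 = 53.

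**Share who cannot complete 2 years.** The last entry date that allows a full 2 years is 31 July 2023. If the 2-year contact may be made 30 days early, it is about 30 August 2023. The recruitment window is 534 days. The article gives no accrual curve, so each row is an assumption.

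| Accrual assumption | Share | Participants |
|---|---|---|
| Uniform, full 2 years: 153/534 | 28.7% | 640 |
| Uniform, contact 30 days early: 123/534 | 23.0% | 515 |
| 400 by end of month 13, 1300 by end of month 19, rest even: 934 × 153/306 | 20.9% | 467 |
| Same, contact 30 days early: 934 × 123/306 | 16.8% | 375 |
| 400/1300/2234 at months 6/12/18 of recruitment, rescaled to the actual window | 35.9% | 803 |
| Rate rising linearly from zero: 1 − (381/534)² | 49.1% | 1097 |

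The month-13 and month-19 figures come from Study progression criteria.

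**Effect on absolute 2-year risks if short follow-up is counted as 24 months.** Late recruits have 19 to 24 months, about 21.5 on average with uniform accrual. Assume a constant hazard.
- Rare events such as death: 1 − 21.5/24 = 10.4% relative shortfall.
- Recurrence at about 40% per year: 1 − 0.6² = 64.0% at 24 months and 1 − 0.6^(21.5/12) = 60.0% at 21.5 months, about 6% relative. With 42.5% per year the fractions are 66.9% and 62.9%, again about 6%.
- Averaged over all participants at a 28.7% late share: 0.287 × 6% = 1.7% for recurrence and 0.287 × 10.4% = 3.0% for rare events.

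**The case against.** The best defence has four parts.

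1. **The main result is safe.** The primary endpoint is at 1 year and the last recruit has 19 months. The 90-day and 1-year secondary endpoints are intact too. This stands.
2. **The arms should be affected alike.** The shortfall depends on calendar date of entry, and allocation is 1:1 and stratified by site. A reader might infer a biased comparison; the document gives no ground for that. This stands.
3. **The analysis of incomplete 2-year follow-up is left to the SAP.** A reader might infer from the choice of logistic regression that late recruits will be dropped or counted as event-free. The article does not say so. It defers missing-data handling, and naming a model does not settle how administratively censored participants are treated. The 2-year counts are to be analysed like the primary, which has an offset. This stands, so the understatement of risk above is conditional.
4. **The completion date is not immovable.** Study progression criteria says that an extension will be considered if recruitment lags. This does not resolve the conflict. It is a contingency, whereas Timelines already reports the actual first recruitment and still gives an end date that does not fit.

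It is also tempting to blame the late first recruitment alone. The month-25 schedule was already one month too long for a 48-month study; the later dates widened the gap to five.

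**Conclusion.** The contradiction is real and follows from the article's own dates: 2 years for everyone cannot be delivered by 31 July 2025 with recruitment open until 31 December 2023.

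Its size is less certain. About 29% is a natural figure to quote, but it assumes uniform accrual and ignores the early side of the visit window. The fair statement is 23% to 29% with uniform accrual, and roughly 17% to 49% over the patterns examined. Every one of them leaves hundreds of participants short. The early window also helps only the 2-year contact; it does not supply two full years of observation.

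The consequence is missing data and lower precision for 2-year secondary endpoints. If short follow-up were counted as 24 months, absolute risks would also be understated among late recruits: about 6% relative for recurrence and up to about 10% for rare events. A 10% understatement across all outcomes is not supported, because that figure is a shortfall in follow-up time and carries over to event fractions only when events are rare.

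Severity: moderate.

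**What to change.** Reconcile Randomisation and interventions, Trial assessments and Timelines in one of two ways.

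1. **Keep 2 years for all.** Move study completion to 31 January 2026 or later, plus time for data cleaning. The cost is about 6 more months of central follow-up and record extraction.
2. **Keep 31 July 2025.** State that follow-up is 2 years or close-out, whichever comes first, with a minimum of 19 months. Then analyse 2-year binary outcomes with a method that accounts for follow-up time (for example time-to-event, or complementary log-log regression with a log follow-up offset), or restrict them to participants with full 2-year follow-up. Make the same choice explicit for 2-year EQ-5D and QALYs: restrict, or model the censoring.

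The second option costs wording and some precision. With uniform accrual, a method based on follow-up time loses about 0.287 × 0.104 = 3% of 2-year person-time. Restriction to the 71% with full follow-up would widen confidence intervals by about 1/√0.713 − 1 = 18%, so it is the dearer choice where the other is available.

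Either change should be made before close-out.

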#### Sample size

Two thousand two hundred and thirty-four participants (1117 standard and 1117 intervention) presenting acutely with syncope whose syncope remains unexplained after initial ED/AMU assessment will be recruited. Using an estimated mean 1-year recurrence rate in untreated patients of 42.5%^6^ and a reduction in 1-year recurrence rate to 10% in patients who are treated^11 19^ then the hypothesis is a 1-year recurrence rate in the standard group (2% diagnosed with a symptomatic significant arrhythmia with 90% of these expected to not have recurrence after treatment) of 40.7% compared with a recurrence rate of 33.1% in the treatment group (10.5% of pilot participants diagnosed with symptomatic significant arrhythmia at 90 days with 90% of these expected to not have recurrence after cardiac arrhythmia treatment) equating to an event rate ratio of 0.81. A more conservative effect size of 6% (40% vs 34%) will be assumed corresponding to a more conservative event rate ratio of 0.85. A large study of unexplained untreated syncope patients^20^ suggests a median (IQR) number of events in the preceding 2 years of 3 (2–4) with a median (IQR) per year of 2 (1–3.5). The ESC guidelines^6^ suggest that the number of events has a good fit to a Poisson distribution and the untreated event rate postattendance is about 70% reduced from the preattendance rate. The ESC guidelines^6^ and PICTURE^20^ suggest a mean number of events per participant of approximately 1 during 1 year of follow-up. If we assume that this follows a negative binomial distribution (which allows for ‘over dispersion’ vs the Poisson distribution) then a study of 1064 participants per group would have 90% power (two-sided significance level=5%, over dispersion=0.25) to detect an event rate ratio of 0.85.

The study will recruit an extra 5% in each arm (ie, 1117 participants per arm; 2234 in total) to allow for drop-out/loss to follow-up although we expect this to be low (<1% in pilot) and drop out due to death (<1% in pilot). It is expected that most people will respond to some text/email follow-ups, but few will respond to all. We will therefore call any participant who has not responded for 3 consecutive months to ensure no syncope episodes have occurred and to encourage continued future engagement. Participants will be defined as lost to follow-up only if both 1-year electronic patient health record data and 1-year self-reported data are unavailable.

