## Introduction

### Background and rationale

Syncope (or blackout) is common; 650 000 patients present to UK emergency departments (EDs) every year. The three underlying causes are neurocardiogenic (including simple faint), postural hypotension (blood pressure fall on standing) and cardiac disease (structural heart disease or cardiac arrhythmia). Diagnosis is difficult and is not made in around 50% of patients after assessment.^1–4^ While vasovagal and postural syncope are relatively benign, serious pathology (affecting 7 out of every 100 patients at 1 month after ED attendance^5^) include arrhythmia (an abnormal heart rhythm). When cardiac arrhythmias are detected, they are most commonly asystolic pauses, reflex bradycardia or advanced atrioventricular block, with tachycardia being the minority.^6^

The difficulty in the ED is to differentiate between the causes of syncope and identify patients at higher risk. This can be complicated as many patients have fully recovered on ED arrival and their examination and presenting ECG may both be normal. The current method for establishing cardiac arrhythmia as the cause of syncope rests on correlating the arrhythmia with symptoms. The lack of efficacy and availability of commonly used monitoring devices means most high and medium risk patients are admitted to the hospital for observation and telemetry (if available), with escalating costs.^1^ Unfortunately, many (around 50% of patients after assessment) still end up being discharged without a diagnosis.^7^

In general, syncope reoccurs in around 50% of patients within a year. Recurring episodes increase hospital admissions, health costs and importantly reduce the quality of life of patients. While there is a wide variation in the literature with respect to the number of syncope episodes and recurrence rates pretreatment and post-treatment^6 8–10^ once a cardiac arrhythmia diagnosis is made and treatment initiated, around only 10% of patients will have a 1-year recurrence^11^ and syncope episodes will drop by over 90%.^11^

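### The 40.7% vs 33.1% (ratio 0.81) benchmark treats every diagnosed patient as certain to recur untreated, so the design ratio of 0.85 is not shown to be conservative

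*Protocol article*

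**What the plan says.** All the design inputs stand in the protocol article's Sample size section.

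- Untreated risk: "Using an estimated mean 1-year recurrence rate in untreated patients of 42.5" per cent.
- Treated risk: "a reduction in 1-year recurrence rate to 10% in patients who are treated".
- Standard arm: "2% diagnosed with a symptomatic significant arrhythmia with 90% of these expected to not have recurrence after treatment) of 40.7" per cent.
- Intervention arm: "compared with a recurrence rate of 33.1% in the treatment group (10.5% of pilot participants diagnosed with symptomatic significant arrhythmia at 90 days", with the same 90% expected to be free of recurrence after treatment.
- The two arm figures are then said to equate to an event rate ratio of 0.81.
- Design effect: "A more conservative effect size of 6% (40% vs 34%) will be assumed corresponding to a more conservative event rate ratio of 0.85".

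The trial is sized at 1064 per group for 90% power at a ratio of 0.85. The calculation uses a negative binomial model with mean about 1 episode per year, overdispersion 0.25 and two-sided 5%. An extra 5% brings this to 1117 per arm. For the count scale, Background and rationale says that after diagnosis and treatment "syncope episodes will drop by over 90" per cent. The Data analysis plan analyses the 12-month episode count by negative binomial regression.

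**The concern.** That 90% of treated patients stay free of recurrence describes their outcome; it is not the effect of treatment. At an untreated risk of 42.5%, 57.5% of them would have stayed free of recurrence anyway. The derivation appears to credit those patients to treatment as well.

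The 0.81 is the only benchmark against which 0.85 is presented as cautious. If 0.81 does not follow from its inputs, the reader has no basis for that description, and the 90% power may refer to a larger effect than the trial's rationale supports. A non-significant result could then be taken as evidence against early monitoring when the trial had little chance of detecting the effect that its own inputs imply.

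**Working it through.** **1. Reproduce the printed recurrence figures.**
- Standard: 42.5 − 0.9 × 2 = 40.7%.
- Intervention: 42.5 − 0.9 × 10.5 = 33.05%, printed as 33.1%.
- Ratio: 33.05 / 40.7 = 0.812.

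Each diagnosed patient therefore removes 90 percentage points. With treated recurrence at 10%, that requires untreated recurrence of 100% in this group.

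**2. Apply the stated fall from 42.5% to 10% (32.5 points), assuming diagnosed patients have the mean untreated risk.**
- Standard: 0.98 × 42.5 + 0.02 × 10 = 41.85%.
- Intervention: 0.895 × 42.5 + 0.105 × 10 = 39.09%.
- Difference 2.8 points; ratio 0.934.

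**3. Same assumption on the count scale, with 90% fewer episodes in diagnosed patients.**
- (1 − 0.105 × 0.9) / (1 − 0.02 × 0.9) = 0.9055 / 0.982 = 0.922.
- Upper bound, with all their episodes abolished: 0.895 / 0.98 = 0.913.

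**4. Reproduce the sample size.** For a negative binomial log rate ratio, with control mean μ0 = 1, μ1 = RR and k = 0.25:

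n per arm = (1.960 + 1.282)² × (1/μ0 + 1/μ1 + 2k) / (ln RR)²

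At RR = 0.85: 10.507 × (1 + 1.1765 + 0.5) / 0.02641 = 1064.8. The stated 1064 is confirmed, with power 90.0%.

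**5. Power at other ratios, 1064 per arm.** Power = Φ(|ln RR| / SE − 1.96), with SE = √[(1 + 1/RR + 0.5) / 1064].

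| Rate ratio | Source | Power |
|---|---|---|
| 0.85 | design value | 90% |
| 0.913 | all episodes abolished, average risk | 45% |
| 0.922 | 90% fewer episodes, average risk | 38% |
| 0.934 | recurrence ratio, if taken as the rate ratio | 28% |

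With all 1117 per arm analysed, the last two become 39% and 30%. A simulation of 3,000 trials with 1064 per arm gave 90%, 37% and 27% at 0.85, 0.922 and 0.934.

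**6. Sensitivity to untreated recurrence u in diagnosed patients.** Overall untreated recurrence is held at 42.5% and treated recurrence at 10%, so the arms are 42.5 − 0.02(u − 10) and 42.5 − 0.105(u − 10), in per cent. Power again takes the recurrence ratio as the rate ratio, as the plan does.

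| u | Standard | Intervention | Ratio | Power |
|---|---|---|---|---|
| 42.5% | 41.9% | 39.1% | 0.93 | 28% |
| 60% | 41.5% | 37.3% | 0.90 | 59% |
| 80% | 41.1% | 35.2% | 0.855 | 88% |
| 100% | 40.7% | 33.1% | 0.81 | 98% |

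**7. What 0.85 requires.**
- Recurrence scale, with d = u − 10% as a proportion: 0.425 − 0.105d = 0.85 × (0.425 − 0.02d). This gives d = 0.06375 / 0.088 = 0.724, so u is about 82%.
- Count scale, with m the diagnosed patients' untreated event rate relative to average: 1 − 0.0945m = 0.85 × (1 − 0.018m). This gives m = 0.15 / 0.0792, about 1.9.

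**The case against.** The strongest reply is that step 2 makes an assumption of its own. The 42.5% is a mean over untreated patients, and the article gives no separate untreated rate for those later found to have a symptomatic arrhythmia. Such patients are selected for symptoms during monitoring and may well recur more often than average. As an illustration, under the plan's mean 1 and overdispersion 0.25, a patient with one syncope in 14 days has an expected rate of 5 / 4.038 = 1.24 times average. That gives a ratio of about 0.90 and power of about 54%. This objection stands: 0.93 is not the one correct answer. It does not rescue the printed figures, which need 100%. Nor can a symptomatic diagnosis be read as certain recurrence. A symptom need not be syncope, and a syncope after randomisation already counts towards the outcome, so later treatment cannot remove it.

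Three smaller points also stand. The drop in episodes is given as over 90%, so 90% is a floor; the abolition bound of 0.913 covers this. Serious arrhythmias without symptoms are also to be managed, so the treated shares may differ from 2% and 10.5%, in a direction the article does not quantify. And 0.85 is indeed closer to 1 than 0.81; the fault lies in the 0.81.

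A reader might infer that the trial's power is 28–38% rather than 90%. The article does not support that as an unconditional statement. It claims 90% power at a ratio of 0.85, and that is correct. The lower figures hold only for average untreated risk in diagnosed patients, and the 28% also puts a ratio of proportions into a formula for counts. A reader might also infer that the futility analysis carries the error forward, but the Interim analysis section states no rule, boundary or target effect. The blinded sample size review in that section does not answer the point either: blinded data would not by themselves reveal an overstated treatment effect.

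**Conclusion.** The point holds in conditional form. The derivation of 40.7%, 33.1% and 0.81 contradicts the fall from 42.5% to 10% in its own sentence, because it silently assumes that every diagnosed patient would recur untreated. This mismatch is arithmetical and certain.

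How far the effect is overstated depends on an unstated quantity, the untreated risk in diagnosed patients. At the stated mean risk the inputs support 2.8 points rather than 7.6, and a rate ratio of about 0.92 with about 38% power. At that risk 0.85 is out of reach even if treatment abolished every episode. If untreated recurrence in diagnosed patients is about 80% or more, 0.85 becomes plausible. The sample size of 1064 per arm is correct for 0.85; what is missing is support for calling that ratio conservative. Because this is the trial's central design effect, it should be corrected.

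**What to change.** - Correct the derivation of 40.7%, 33.1% and 0.81, and state the untreated recurrence or event rate assumed for diagnosed patients, with its justification.
- Derive the effect on the count scale of the primary outcome, rather than carrying a ratio of recurrence proportions over as an event rate ratio.
- Remove the description of 0.85 as more conservative unless the assumption behind it is justified: about 82% untreated recurrence, or about 1.9 times the average event rate, in diagnosed patients.
- Restate power as 90% at 0.85 only, and add power over the range of ratios that the stated inputs support, including about 38% at 0.92.

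The cost is protocol wording, and a statement of power that reads less favourably. The correction needs no extra patients.

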#### Interim analysis

In addition to the blinded sample size review to ensure that the trial achieves the required statistical power, there will be a single interim futility analysis for the primary outcome performed after the 18th month of recruitment (end of study month 25). At this point 6 months of 1-year follow-up data will be available. We anticipate at least 400 participants will have undergone 12-month follow-up for the primary outcome at this point and will be able to be analysed in this futility analysis.

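### The sample size mixes inconsistent inputs: mean 1 with dispersion 0.25 implies 59% of controls recur, yet the 0.85 ratio comes from 40%, so the 90% power does not hold at the plan's own recurrence rates

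*Protocol article*

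**What the plan says.** All the inputs stand in one section of the protocol article, Sample size.

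- **Effect.** The target ratio is taken from recurrence proportions: "A more conservative effect size of 6% (40% vs 34%) will be assumed corresponding to a more conservative event rate ratio of 0.85". Recurrence here means the share of patients with at least one further episode, because the derivation counts patients, "with 90% of these expected to not have recurrence after treatment". The same section gives 42.5% for untreated patients and 40.7% as the hypothesised standard-care figure. The Introduction gives about 50%.
- **Count model.** Two cited sources are said to "suggest a mean number of events per participant of approximately 1 during 1 year of follow-up", and a negative binomial distribution is assumed for that count.
- **Result.** "then a study of 1064 participants per group would have 90% power (two-sided significance level=5%, over dispersion=0.25") "to detect an event rate ratio of 0.85". A 5% allowance brings this to 1117 per arm.

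The Interim analysis section adds one clause on a safeguard: "In addition to the blinded sample size review to ensure that the trial achieves the required statistical power".

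**The concern.** In a negative binomial model, the mean and the dispersion together fix the proportion of patients with no episode. Once mean 1 and dispersion 0.25 are chosen, the control recurrence proportion is no longer free. If it differs from the 40% that produced the ratio, the effect size and the variance in the power calculation describe two different populations.

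Power for the primary outcome is at stake. A lower recurrence proportion means either fewer episodes or more overdispersion. Both widen the standard error of the log rate ratio and lower the power at a ratio of 0.85.

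**Working it through.** **Inputs** (Sample size section unless noted): two-sided 5%, 90% power, rate ratio RR = 0.85, control mean μ = 1, dispersion k = 0.25, 1064 per group, 1117 recruited per group. Recurrence: 40% assumed, 42.5% untreated, about 50% (Introduction).

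**1. Reproduce the plan's figure.** For a Wald test on the log rate ratio:

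n = (1.960 + 1.2816)² × [1/μ + 1/(μ·RR) + 2k] / (ln RR)²

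n = 10.507 × (1 + 1.1765 + 0.5) / 0.02641 = 10.507 × 2.6765 / 0.02641 = 1064.8

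Power at 1064 is 89.98%, so the stated 1064 and 90% follow from these inputs.

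**2. Recurrence implied by those inputs.** P(at least one) = 1 − (1 + kμ)^(−1/k).

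- Control: 1 − 1.25^(−4) = 59.0%, against 40% assumed.
- Intervention, mean 0.85: 1 − 1.2125^(−4) = 53.7%, against 34% assumed.

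**3. Reconcile by moving one input at a time.** Either keep μ = 1 and solve for k, or keep k = 0.25 and solve for μ. Then, with V = 1/μ + 1/(μ·0.85) + 2k,

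power = Φ( |ln 0.85| × √(n/V) − 1.960 )

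| Control recurrence | μ | k | Power, 1064 per group | Power, 1117 per group | n per group for 90% |
|---|---|---|---|---|---|
| 40% | 1 | 2.39 | 52.0% | 54.0% | about 2770 |
| 40% | 0.545 | 0.25 | 70.6% | 72.6% | 1788 |
| 42.5% | 1 | 1.96 | 57.4% | 59.4% | about 2430 |
| 42.5% | 0.593 | 0.25 | 73.8% | 75.8% | 1658 |
| 50% | 1 | 1.00 | 73.7% | 75.7% | about 1660 |
| 50% | 0.757 | 0.25 | 82.3% | 84.0% | 1343 |

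First row worked through: V = 1 + 1.1765 + 4.780 = 6.956; 0.1625 × √(1064/6.956) = 2.010; Φ(2.010 − 1.960) = 52.0%.

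Simulation with maximum-likelihood dispersion (1500 trials per setting) gives 53.8% and 69.1% for the two 40% rows, and 89.7% for the plan's own inputs.

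**4. Ratio detectable with 90% power.** Solving the formula for RR at 40% recurrence and 1064 per group gives 0.77 (μ = 1, k = 2.39) to 0.81 (μ = 0.545, k = 0.25).

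**5. Can 40% versus 34% and a ratio of 0.85 hold together?** Yes, under the mechanism the plan describes, in which a fraction of patients is treated and stops having episodes. If 15% of the intervention arm has no further episodes, recurrence is 0.85 × 40% = 34% and the mean falls by the same factor. Simulated power at 1064 per group (2000 trials) is then 49% (μ = 1, k = 2.39) and 68% (μ = 0.545, k = 0.25).

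**The case against.** **The 90% is not an arithmetic error.** This stands. Recurrence does not enter the power formula, and the mean and dispersion reproduce 1064. If mean 1 and dispersion 0.25 are true and the 40% is wrong, power remains 90%. The documents do not settle which input is at fault. That resolution, however, needs 59% recurrence, and no figure in the article reaches it.

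**The 52% to 71% range is conditional.** This also stands. It requires 40% recurrence, a ratio of 0.85, 1064 evaluable per group and one input moved at a time. A reader might take it as the trial's true power. The article's recurrence figures run up to about 50%, where power is 74% to 82%. The ratio of 0.85 is itself set conservatively against a hypothesised 0.81. At 0.81 with 40% recurrence, the same formula gives 74% (μ = 1, k = 2.39) or 89% (μ = 0.545, k = 0.25).

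**Imposing 40% and 34% on two negative binomials with a common dispersion gives stronger ratios.** These are 0.80 at k = 0.25 (power 91%) and 0.71 at k = 2.39 (power 99%). But the plan powers for 0.85, and its own mechanism keeps 40%, 34% and 0.85 compatible, with power of 49% to 68%.

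**A reader might infer that the mean of 1 is itself wrong**, because the section reports a median of 2 episodes per year and says "the untreated event rate postattendance is about 70% reduced from the preattendance rate", and 2 × 0.3 = 0.6. The documents do not support this. The cut is being applied to a median with quartiles 1 and 3.5, which is right-skewed, so the mean before the cut may well be above 2. The figures therefore do not exclude a mean near 1.

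**A blinded review is planned.** It could detect a wrong mean or dispersion, which mitigates the problem but does not make the stated inputs agree. A reader might also infer that the review will come too late to help. The article gives it no date, and the 12-month wording in the Interim analysis section belongs to the separate futility analysis, so lateness is conjecture.

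**Conclusion.** The point holds as an inconsistency of assumptions. The ratio rests on 40% of controls recurring, while the sample size rests on a distribution in which 59% recur. The 90% is correct for its own inputs but does not hold under any recurrence rate the article gives. At ratio 0.85 and 1064 per group, power is about 52% to 71% at 40% recurrence, 57% to 74% at 42.5% and 74% to 82% at 50%. With all 1117 per group evaluable, each figure rises by about 2 points.

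These figures assume a negative binomial count with the same dispersion in both arms, a true ratio of 0.85, full one-year follow-up, and reconciliation through either the mean or the dispersion alone. They do not show that the trial is underpowered in fact; that depends on the mean, dispersion and effect that actually occur. Because the 90% is the power claim for the primary outcome, it should be corrected.

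**What to change.** 1. Reconcile the mean, dispersion and recurrence inputs in the Sample size section, and say which is taken as primary and why.
2. Restate power at 0.85 as a range over mean and dispersion pairs that reproduce the assumed recurrence. At 40% this is about 52% to 71% with 1064 per group. Alternatively, state the ratio detectable with 90% power, about 0.77 to 0.81.
3. Specify that the blinded review already planned estimates the pooled mean and dispersion from the accrued 4-weekly participant reports while recruitment is still open.

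The cost is a change of wording and a less favourable stated power. The 4-weekly reports are already collected from all participants, so no new data are needed. Restating power does not raise it, and the review may show that 90% at a ratio of 0.85 needs more participants than planned.
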